## Abstract

**Background:**

The COVID-19 pandemic has led to worldwide implementation of unprecedented restrictions to control its rapid spread and mitigate its impact. The Spanish government has enforced social distancing, quarantine, and home confinement measures. Such restrictions on activities of daily life and separation from loved ones may lead to social isolation and loneliness with health-related consequences among community-dwelling older adults with mild cognitive impairment or mild dementia and their caregivers. Additionally, inadequate access to health care and social support services may aggravate chronic conditions. Home-based technological interventions have emerged for combating social isolation and loneliness, while simultaneously preventing the risk of virus exposure.

**Objective:**

The aim of this cohort study is to explore, analyze, and determine the impact of social isolation on (1) cognition, quality of life, mood, technophilia, and perceived stress among community-dwelling older adults with mild cognitive impairment or mild dementia and on the caregiver burden; (2) access to and utilization of health and social care services; and (3) cognitive, social, and entertainment-related uses of information and communication technologies.

**Methods:**

This study will be conducted in Málaga (Andalucía, Spain). In total 200 dyads, consisting of a person with mild cognitive impairment or mild dementia and his/her informal caregiver, will be contacted by telephone. Potential respondents will be participants of the following clinical trials: support, monitoring, and reminder technology for mild dementia (n=100) and television-based assistive integrated service to support European adults living with mild dementia or mild cognitive impairment (n=100).

**Results:**

As of May 2021, a total of 153 participants have been enrolled and assessed during COVID-19 confinement, of whom 67 have been assessed at 6 months of enrollment. Changes in the mean values of the variables will be analyzed relative to baseline findings of previous studies with those during and after confinement, using repeated-measures analysis of variance or the nonparametric Friedman test, as appropriate. The performance of multivariate analysis of covariance (ANCOVA) to introduce potential covariates will also be considered. Values of 95% CI will be used.

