### Statistical Analysis

The flow of participants will be shown schematically with counts and percentages in a CONSORT diagram. All variables collected will be summarized at baseline and at follow-up. Statistics considered for presentation for continuous measures in summary tables include the mean (SD), minima, and maxima, and if the criteria of normality are not met, the median and the first and third quartiles will be recorded. Categorical variables will be summarized as counts and percentages.

The change in means in the study variables will be analyzed in accordance with the results of previous trials (SMART4MD and TV-AssistDem) with those currently collected using repeated-measures analysis of variance or the nonparametric Friedman test as appropriate. The performance of multivariate analysis of covariance (ANCOVA) to introduce possible covariates will also be considered. A 95% CI will be used for all comparisons. R (version 3.6.1, The R Foundation) will be used for all statistical analysis [39].

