## Discussion

If our study hypothesis is accepted, these findings will demonstrate the negative impact of social isolation due to COVID-19 confinement on cognition, QoL, mood, and perceived stress, and technophilia in community-dwelling older PMCI/MDs, caregiver burden, and the access to and utilization of health and social care services, along with the cognitive, social, and entertainment-related use of ICTs during and after COVID-19 confinement.

Our findings will help assess the adoption of dementia technology by older people and their caregivers during the COVID-19 pandemic and may help alleviate the impact of present and future confinements in different aspects of their daily lives.

The preparedness and responses of governments to situations of the magnitude of COVID-19 will help determine related outcomes and consequences, which extend beyond the disease itself, with political, economic, cultural, health-related, and social impacts compromising the QoL of all. These responses, which include enforcing restrictive measures, lead to social isolation, which, in the context of an ecological framework, has an impact at the individual, relationship, community, and societal levels [4].

At an individual level, those with personal characteristics such as old age, life-course transitions, and health decline [10], particularly those with a diagnosis of dementia [3], are at higher risk. Abrupt and forced social isolation may be considered a disruptive event among older people and may predispose them to psychological distress [10]. Not being able to take part in daily activities, loss of usual routine, and nonattendance to memory workshops and day care services under closure may worsen cognition and functioning in this population. Daily activities such as going to grocery stores and pharmacies, may be carried out by caregivers to prevent risk of exposure, thus increasing caregiver burden.

At a relationship level, social distancing has compromised the reliability of social networks and the frequency of contact with others. Inadequate social support, when most needed, may aggravate depressive symptoms [12].

At a community level, interventions for the provision of health care and social support services are limited to prevent risk exposure, causing direct and indirect impacts on the prevention of ill health, promotion of health, and lifelong management and treatment of diseases.

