### Limitations

Although telephonic interviews would be the safest means to communicate with the dyads during the COVID-19 pandemic, there will be several drawbacks. The amount of information gathered and provided on a single telephone call is limited and researchers will have to balance the time spent on each call. Moreover, the assessment of cognition will be partial as the language section of the MMSE requires the assessment of visual and motor skills, which cannot be accomplished through a telephone call. Although evidence for telephone-based cognitive assessment recommends using the telephone interview for cognitive status instrument and its modified version [41,42], the study population undertook the MMSE thrice over a period of 1 year prior to this study, thus providing relevant data to compare their decline before confinement (baseline data) and afterwards. Furthermore, overloading PMCI/MDs with a long interview is not advisable as it may feel tedious and time-consuming. Finally, older people may have hearing impairments, which may make telephone assessments difficult. Caregiver assistance will be requested to complete the interviews.

The assessments in this study involve minimal risk to the patients. To ensure the standardization of interventions, researchers have received web-based training on the standard operating procedure, which includes a working plan, different aspects of the study, the protocol scheme to identify the appropriate measures, and the details to assess each variable safely among older adults. This will guarantee that the procedure can be replicated elsewhere.

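### The planned T0/T1/T2 comparison of means does not make the before-and-after comparison of MMSE decline that Limitations promises, so ordinary progression cannot be separated from a confinement effect

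*Protocol article*

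**What the plan says.** The analysis is described twice. The Abstract (Results) has "Changes in the mean values of the variables will be analyzed relative to baseline findings of previous studies"; the values set against that baseline are those at T1 and T2. The Statistical Analysis section has "The change in means in the study variables will be analyzed in accordance with the results of previous trials" and, for the choice of test, "with those currently collected using repeated-measures analysis of variance or the nonparametric Friedman test as appropriate". ANCOVA with covariates is to be considered but is not committed to.

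Outcome Measures defines one pre-confinement occasion, T0, to be compared with T1 (during confinement) and T2 (6 months). Table 1 likewise has a single baseline column. Respondents come from both arms of the two parent trials, and the whole cohort is assessed under the national lockdown.

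Limitations concedes that other instruments are recommended for telephone testing, but keeps the MMSE because "the study population undertook the MMSE thrice over a period of 1 year prior to this study". The use foreseen for those earlier scores is given in the same sentence: "thus providing relevant data to compare their decline before confinement (baseline data) and afterwards".

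On interpretation, the Discussion says that, if the hypothesis is accepted, "these findings will demonstrate the negative impact of social isolation due to COVID-19 confinement on cognition". The Abstract (Conclusions) says the same in nearly the same terms.

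**The concern.** In people with mild cognitive impairment or mild dementia, some fall in mean MMSE over the months from T0 to T2 is expected without any lockdown. The null hypothesis under test is that the mean does not change over time. The question the study asks is whether the course departed from the one these people were already on. With everyone exposed and one pre-confinement mean, rejecting the first null says little about the second.

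Limitations shows that the authors saw the need for a before-and-after comparison of decline and chose the primary instrument partly for that reason. The analysis as written does not use that advantage. At stake are the reading of the primary outcome and the main conclusion of the study.

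**Working it through.** **Side by side.**

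| Place | What it sets |
|---|---|
| Limitations | Three MMSEs in the year before the study, for comparing decline before and after |
| Outcome Measures, Table 1 | One pre-confinement occasion (T0), then T1 and T2 |
| Abstract (Results), Statistical Analysis | Change in means by repeated-measures ANOVA or Friedman; no slope, elapsed-time or expected-decline term |
| Covariables | Neither prior slope nor time since T0 is listed |
| Abstract (Conclusions), Discussion | Change would be read as the impact of isolation |

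**No stated figure to reproduce.** The article gives no effect size, SD, decline rate or T0–T1 interval. The numbers below are illustrations under stated assumptions.

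**Inputs from the article:** 153 participants assessed at T1 and 67 at 6 months (taken here as the numbers with MMSE data); 95% confidence level (two-sided 0.05). **Assumed:** natural decline r points/year, SD of the T0–T1 change s, gap g months, and no confinement effect.

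**Formula.** Expected fall d = r × g/12; z = d/(s/√n); rejection probability = Φ(z − 1.96) + Φ(−z − 1.96).

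With s = 3, the standard error is 3/√153 = 0.2425 (n=153) and 3/√67 = 0.3665 (n=67). With r = 0.5:

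| Gap | d | z, n=153 | Rejects, n=153 | z, n=67 | Rejects, n=67 |
|---|---|---|---|---|---|
| 3 months | 0.125 | 0.515 | 8% | 0.341 | 6% |
| 6 months | 0.250 | 1.031 | 18% | 0.682 | 10% |
| 14 months | 0.583 | 2.405 | 67% | 1.592 | 36% |

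With r = 1 and s = 3, n=153 gives 18%, 54% and 99.8% for the same three gaps, and n=67 gives 10%, 28% and 89%. The nominal rate is 5%.

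**Adding T2.** T2 brings in six more months of progression. A simulation (2,000 runs per setting) assumed three pre-confinement scores at −12, −6 and 0 months with T0 the last of them, T1 at 6 or 12 months after T0 and T2 six months later, between-person SD 3, slope SD 1 point/year, residual SD 1.5 and linear decline. With no confinement effect:

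- Repeated-measures ANOVA on T0/T1/T2 rejected in 34–92% of runs at 0.5 points/year and in 90–100% at 1–2 points/year.
- Comparing T1 and T2 with each person's line projected from the three earlier scores rejected in 4.4–5.8% of runs at every decline rate from 0 to 2 points/year, for n=67 and n=153.

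The simulation contains no telephone-mode effect and generates truly linear decline, so it shows that the trend comparison removes this one problem, not every problem.

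**The case against.** The strongest reply is that the plan already intends the right comparison. Limitations names it and labels the pre-confinement decline as baseline data. The Statistical Analysis section refers to results of the previous trials rather than to one visit. Repeated-measures ANOVA can take more than three occasions, and a condensed article may leave the model to a separate analysis plan. This has force against a reader who infers that the document ignores the earlier MMSEs: it does not. But the article fixes the contrast (change in means), the occasions (T0, T1, T2) and the tests, and these do not deliver what Limitations describes.

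A second reply is that ANCOVA may be used. It is only to be considered, and when everyone is exposed over the same period, adjusting for personal characteristics does not separate a shared time trend from a confinement effect.

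A third is that the inflation may be small. This stands as a limit on size. The article does not say which MMSE is T0. If it is the last one and the gap is short, the test may reject little more often than 5%. A reader might assume T0 is the first of the three and conclude that most of the T0–T1 interval predates confinement; the text does not establish that.

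A reader might also infer that all change will be reported as harm. The conclusions are conditional on the hypothesis being accepted and the stated aim is to explore, so the supportable statement is that progression cannot be separated from confinement and may be misread as its effect. Nor does the lack of an unexposed group show poor planning, since the lockdown was nationwide.

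Finally, one might take living alone as a direct marker of isolation, since living arrangements are collected. The Introduction defines isolation as absence of contacts, interactions or relationships, so living alone is a proxy at best.

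**Conclusion.** The point holds as a mismatch within the article. The reason given for keeping the primary instrument is a comparison of decline before and after confinement, and the stated analysis is a comparison of means from a single baseline in a wholly exposed cohort. A fall from T0 would not support the attribution to isolation made in the Abstract (Conclusions) and Discussion.

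The size is uncertain. With no confinement effect, SD 3 and 0.5 points/year, the T0–T1 test at n=153 rejects from about 8% (3-month gap) to 67% (14 months), and more often with faster decline or a smaller SD. Gap, decline rate and SD are assumptions. Because the mismatch bears on the primary outcome and the headline conclusion, it should be corrected before analysis. The trend-based analysis is better but does not isolate a clean confinement effect, because the move to the telephone MMSE coincides with confinement.

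**What to change.** In Statistical Analysis:

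- Make the primary MMSE analysis a mixed or segmented model with all pre-confinement MMSEs plus T1 and T2, using actual time in months.
- Score every occasion on the items common to the 22-item telephone version, where item-level parent-trial data are available. The article does not say that they are.
- Make the estimand the departure of T1 and T2 from the projected pre-confinement trend.
- State which parent-trial visit is T0 and report the T0–T1 interval.

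Three pre-confinement measurements are documented for the MMSE only. For outcomes without documented repeated earlier values, report change over the period. Reword the Abstract (Conclusions) and Discussion so that such change is not said to demonstrate an effect of isolation.

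The work is linkage of parent-trial visits, rescoring and revised wording. The statistical costs should be stated in the plan:

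- **Wider interval.** In the simulation set-up with a 6-month gap, the average of T1 and T2 falls 0.75 years after T0. The person-level SD of the projected contrast is 1.5 × √(1/3 + 1.25²/0.5 + 1/2) = 2.98. For the raw change from T0 it is √(1.5² × 1.5 + 1² × 0.75²) = 1.98. The interval is therefore about 1.5 times as wide.
- **Linear-trend assumption.** Three points over one year give little means of checking it.
- **Mode effect.** Any difference between telephone and earlier administration would appear as a level change at the start of confinement, and common-item scoring reduces this only in part.

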**Conclusions:**

If our hypothesis is accepted, these findings will demonstrate the negative impact of social isolation owing to COVID-19 confinement on cognition, quality of life, mood, and perceived stress among community-dwelling older adults with mild cognitive impairment and mild dementia, the impact on technophilia, caregiver burden, the access to and utilization of health and social care services, and the cognitive, social, and entertainment-related use of information and communication technologies during and after COVID-19 confinement.

**Trial Registration:**

ClinicalTrials.gov NCT04385797; https://clinicaltrials.gov/ct2/show/NCT04385797

**International Registered Report Identifier (IRRID):**

DERR1-10.2196/26431

## Introduction

The COVID-19 pandemic has forced government authorities worldwide to implement unprecedented restrictions to control its rapid spread and mitigate its impact [1]. In response to the outbreak, Spain declared, by royal decree (463/2020), a national emergency, with the exceptional measure of a nationwide lockdown enforcing social distancing, quarantining of those exposed to the virus, and home confinement of those who remain healthy, while allowing only essential outings [2]. This home-confinement by restricting movement to carry out activities of daily life and social distancing from loved ones may be a challenging and unpleasant experience for those who undergo it, leading them to experience social isolation and loneliness and having health-related consequences. Vulnerable populations at a higher risk are fragile community-dwelling older adults whose chronic conditions may be aggravated by the consequences of the confinement and, in particular, people with mild cognitive impairment or mild dementia (PMCI/MD) [3].

Social isolation (the absence of social contacts, interactions, or relationships with other individuals including family, friends, or neighbors) and loneliness (perception of isolation or feeling of being lonely) have been well established as risk factors for health-related consequences and quality of life (QoL) [4] (an individual's perception of their position in life in a cultural context in relation to their goals, expectations, standards, and concerns [5], including physical and mental health, social relationships, and participation in activities).

Numerous observational studies have reported associations between social isolation and an increased risk of dementia and cognitive decline in older adults [6-8]. Reduction of social contacts and lower levels of participation in social activities are associated with declines in global cognition, processing speed, executive function, and visuospatial abilities [9].

Facing novel and unknown situations is a potential stressor, especially when cognition may be compromised [10], and loneliness may help predict changes in depressive symptomatology [11]. A systematic review on social relationships and depression in later life, which included 37 studies (25 cross-sectional and 12 longitudinal studies), reported that having a decreased social network was significantly associated with depression in older adults [12].

Social isolation is likewise associated with a higher prevalence of other comorbid conditions including cardiovascular diseases [13], stroke [13], and the risk of premature mortality [14]. Furthermore, studies on social isolation and health-related behaviors have reported that older people who are isolated are more likely to have less health-related behaviors such as poor diets, tobacco use, heavy alcohol use, and a lack of physical activity [6,15].

The burden of COVID-19 exerts pressure on health care and social support services [2] and caregivers. Spain’s health care system is struggling to deliver emergency and intensive care. Routine interventions for service provision, such as primary and specialist care consultations, diagnostic testing, and nonemergency interventions, have been cancelled, postponed, or their delivery has shifted from an in-person to a technology-based format. Additionally, caregivers’ burden may be worsened in an attempt to reduce the risk of virus exposure among their care recipients.

In the information age, with the increased use of information and communication technologies (ICTs), home-based technological interventions [16] including smartphones, tablets, computers, smart televisions, virtual assistants, and ambient assistive devices have emerged for combating social isolation and loneliness. A challenge associated with these interventions is that vulnerable populations at a higher risk of becoming severely socially isolated owing to the COVID-19 pandemic, such as older people, may have negative attitudes and lack of enthusiasm toward the use of ICTs, thus having low technophilia [17]. Technophilia is described as the “attraction, enthusiasm of the human individual determined by the activities which involve the use of advanced technologies. It is expressed by easy adaptation to the social changes brought by technological innovations” [18].

International recommendations stress the need to urgently identify the needs of people with dementia and their caregivers and establish technological strategies for their assistance and support [19]. In response to the COVID-19 pandemic, studies have shown increased interest in technology among people with dementia [20] and have emphasized the challenges associated with the adoption of technology-based interventions by people with dementia [21], but few studies have explored the impact of technologies on social isolation in this population.

The aims of this study are threefold: (1) to explore the impact of social isolation on cognition, QoL, mood, technophilia, and perceived stress of community-dwelling older PMCI/MD and on caregiver burden; (2) to investigate how social isolation affects the access to and utilization of health care and social support services; and (3) to determine the health-related, cognitive, social, informative, and entertainment-related uses of ICTs during and after 6 months of COVID-19 confinement.

## Methods

### Study Design

This cohort study will be conducted in Málaga (Andalucía, Spain). The study will assess Cognitive Outcomes During COVID-19 confiNemeNt in Elderly and Their Caregivers Using Technologies for DEMentia (CONNECTDEM). Interviews will be conducted telephonically to guarantee the safest means to communicate during the COVID-19 pandemic. Researchers will contact participants by telephone, explain the study in detail, answer any questions which may arise, and ask those who are willing to participate in the study to provide consent. Interviews were conducted in May 2020. Follow-up assessments would be carried out after 6 months.

### Setting

Participants will be identified from the support, monitoring, and reminder technology for mild dementia (SMART4MD; trial# NCT03325699) [22] and television-based assistive integrated service to support European adults living with mild dementia or mild cognitive impairment (TV-AssistDem; trial# NCT03653234) [23] clinical trials, both of which aim to assess the effects of ICTs to support dementia by using a tablet-based health app and a television-based assistive integrated service, respectively. Participants will include people with self-perceived cognitive impairment or their caregiver’s perception of cognitive impairment that has been present for >6 months under primary and secondary care services, including those who are being followed-up at memory clinics, outpatient clinics, day hospitals, or other components of specialist mental health, geriatric medicine, and neurology services.

